**Methods/Design:**

The Intra-peritoneal Vacuum Trial will be a single-center, randomized controlled trial. Adults will be intraoperatively allocated to TAC with either the ABThera or Barker’s vacuum pack after the decision has been made by the attending surgeon to perform a damage control laparotomy. The study will use variable block size randomization. On study days 1, 2, 3, 7, and 28, blood will be collected. Whenever possible, peritoneal fluid will also be collected at these time points from the patient’s abdomen or TAC device. Luminex technology will be used to quantify the concentrations of 65 mediators relevant to the inflammatory response in peritoneal fluid and plasma. The primary endpoint is the difference in the plasma concentration of the pro-inflammatory cytokine IL-6 at 24 and 48 h after TAC dressing application. Secondary endpoints include the differential effects of these dressings on the systemic concentration of other pro-inflammatory cytokines, collective peritoneal and systemic inflammatory mediator profiles, postoperative fluid balance, intra-abdominal pressure, and several patient-important outcomes, including organ dysfunction measures and mortality.

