### Data collection

#### Peritoneal fluid and blood

On study day 1, just before application of the allocated TAC dressing, 4 mL of peritoneal fluid and 16 mL of blood will be collected. Peritoneal fluid will be taken directly from the peritoneal cavity and then transferred into sodium-heparin-containing vacutainer tubes (Benton Dickinson Biosciences, Oakville, ON, Canada). Blood will be collected from the patient’s indwelling intravascular catheter or via venipuncture into sodium-heparin containing and clot-activating (serum collection) vacutainer tubes (Benton Dickson Biosciences, Oakville, ON, Canada). Sixteen mL of blood will also be drawn on study days 2, 3, and 7, as well as on study day 28 or at hospital discharge (whichever comes first). Whenever possible, 4 mL of peritoneal fluid will also be removed at these times from the tubing set or Jackson-Pratt drainage tubing among patients fitted with an ABThera™ or Barker’s vacuum pack, respectively. Immediately after collection, blood and peritoneal fluid samples will be gently inverted several times and then immediately spun at 1,200 g for 15 min at 4°C in a swinging bucket centrifuge to remove cellular debris. The cell-free supernatants will subsequently be collected, aliquoted into labeled cryopreservation tubes, and frozen at −80°C until laboratory analyses can be performed.

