### Study endpoints

#### Primary endpoints

As the pro-inflammatory cytokine IL-6 is consistently upregulated following intra-abdominal sepsis or injury and has been reported to correlate with outcomes (Table 
2), the primary endpoint is the difference in the plasma concentration of IL-6 at 24 and 48 h after dressing application between patients randomized to TAC with the ABThera™ *versus* Barker’s vacuum pack after damage control laparotomy.

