### Statistical analyses

All continuous variables will be summarized using histograms and measures of central tendency to determine their underlying distribution before statistical descriptions or analyses are conducted. Means (with standard deviations) and medians (with interquartile ranges) will be used to summarize normal and skewed data, respectively. Non-correlated means and medians will be compared using t-tests and Wilcoxon rank sum tests while dependent means and medians will be compared using paired t-tests and Wilcoxon signed rank tests. Differences in proportions will be compared using Fisher’s exact test and risk ratios with associated 95% confidence intervals.

For the analysis of the primary endpoint, we will use a mixed-effects repeated measures linear model to compare the effects of the ABThera™ and Barker’s vacuum pack on changes in plasma IL-6 concentration at 24 and 48 h after TAC dressing application
[75,76]. For longitudinal studies, mixed-effects models have previously been shown to be superior to conventional last-observation-carried-forward approaches for handling missed observations during follow-up
[77,78]. This approach will also be used to compare the plasma concentrations of TNF-α and IL-1, -8, -10, and −12 between groups at 24 and 48 h in the analysis of secondary endpoints.

Multidimensional analysis will be used to assess whether the allocated TAC dressing has an effect on the collective peritoneal and plasma mediator profiles of the study patients. Principal components analysis will be used to reduce the mediator concentration variables into a smaller set of components that account for most of the variability in the data. Component scores will subsequently be calculated along the reduced number dimensions, after which we will attempt to distinguish between patients treated with the ABThera™ and Barker’s vacuum pack using discriminant or latent class analysis. A similar approach will be performed in order to relate inflammatory mediator concentrations to outcomes.

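### The primary endpoint is defined as an IL-6 level but analysed as a change, and the role of the pre-dressing sample is not fixed; adjusting for that sample gives a more precise estimate

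*Protocol article*

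**What the plan says.** Under Primary endpoints the article states that "the primary endpoint is the difference in the plasma concentration of IL-6 at 24 and 48 h after dressing application" is compared between the two arms. The Methods/Design paragraph of the abstract agrees: "The primary endpoint is the difference in the plasma concentration of the pro-inflammatory cytokine IL-6 at 24 and 48 h". Both describe a level, and neither mentions a baseline or a change.

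Under Statistical analyses, for the same endpoint, "we will use a mixed-effects repeated measures linear model to compare the effects" of the two dressings "on changes in plasma IL-6 concentration at 24 and 48 h after TAC dressing application". No reference time is named. Two sentences later the wording returns to levels for TNF-α and the other secondary interleukins: "This approach will also be used to compare the plasma concentrations of" these mediators.

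A baseline value is planned. The subsection on peritoneal fluid and blood sampling states: "On study day 1, just before application of the allocated TAC dressing, 4 mL of peritoneal fluid and 16 mL of blood" are to be collected. The article does not say whether this value is subtracted, enters as a covariate, or is one of the repeated responses. The same analysis section assigns mediator data to a per-protocol set, defined by the allocated dressing having stayed in place for at least 24 h.

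**The concern.** The two statements of the primary comparison disagree on what is compared, and the second does not say how the baseline is handled. In a trial of 46 patients, a chance difference in pre-dressing IL-6 between arms is likely to be noticeable. A level analysis ignores that difference, a change analysis subtracts all of it, and an adjusted analysis removes the part that predicts follow-up. One data set can therefore give different primary estimates and p-values, and the document does not settle which one counts.

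Precision is also at stake. The Discussion concedes that the trial may be underpowered for the mediator comparisons. A change contrast carries baseline noise that an adjusted contrast avoids, although both use the same blood sample.

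**Working it through.** **Inputs from the article.** 46 patients (Sample size). Equal allocation is intended (Patient randomization), so 23 per arm. Tests are two-sided (Statistical analyses). No effect size, SD, correlation or missing-sample rate is given, and 46 is a convenience sample, so there is no stated power to reproduce.

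**Assumptions.** SDs are s0 before the dressing and s1 at follow-up, on the scale on which IL-6 is modelled. The correlation is rho, shown at 0.3, 0.5 and 0.7. The formulas are large-sample and ignore the small cost of estimating the baseline slope.

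**Step 1: how far level and change estimates can differ.** If the arms differ by D0 at baseline and D1 at follow-up, the level estimate is D1 and the change estimate is D1 − D0. The gap is D0. Under randomization its expectation is 0 and its standard error is √(2/23) = 0.295 baseline SDs. The two analyses agree on average but can differ appreciably in a single trial of this size.

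**Step 2: variance per patient.**
- Change: s0² + s1² − 2·rho·s0·s1
- Adjusted for baseline: s1²(1 − rho²)
- Change minus adjusted: s0² − 2·rho·s0·s1 + rho²·s1² = (s0 − rho·s1)²

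The excess is never negative. It is zero only when s0 = rho·s1.

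**Step 3: equal SDs.** Relative to a level comparison (variance 1), change has 2(1 − rho) and adjusted has 1 − rho², a ratio of 2/(1 + rho).

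| rho | change | adjusted | ratio | 46 ÷ ratio |
|---|---|---|---|---|
| 0.3 | 1.40 | 0.91 | 1.54 | 29.9 |
| 0.5 | 1.00 | 0.75 | 1.33 | 34.5 |
| 0.7 | 0.60 | 0.51 | 1.18 | 39.1 |

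With equal SDs, change is worse than ignoring baseline when rho is below 0.5. In general the threshold is rho < s0/(2·s1).

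**Step 4: power, for illustration only.** With an assumed 0.8 SD difference, 23 per arm, nominal two-sided 0.05 and a normal approximation, power for level / change / adjusted is 77% / 63% / 81% at rho 0.3, 77% / 77% / 88% at rho 0.5, and 77% / 94% / 97% at rho 0.7.

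**Step 5: missed baselines.** Take rho 0.5 between every pair of times and assume 20% of baselines are missing completely at random. Standard errors of the 24 h effect, in SD units:
- computed change, complete cases: 0.330
- mixed model with baseline among the responses and free baseline means, change contrast: 0.319
- baseline as covariate, complete cases: 0.286
- constrained baseline (common baseline mean for both arms): 0.261

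With no baselines missing, the first two are both 0.295 and the last two are both 0.255. The second model keeps patients without a baseline but is still less precise: (0.319/0.261)² ≈ 1.5 times the variance of the constrained model.

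**The case against.** The strongest reply is that the article names a mixed model and never mentions subtraction. Its wording fits a treatment-by-time model with the day-1 value among the responses, and the switch between changes and concentrations within one paragraph suggests loose phrasing. This is fair, and a computed change score cannot be read into the text as fact. It does not remove the point. With free baseline means, the treatment-by-time contrast has the same variance as the change score when data are complete, and the endpoint definition still says level.

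A reader might also infer that patients whose intraoperative sample was missed will be lost. The document does not show this. A mixed model with baseline as a response keeps them. The Discussion's remark about night-time operations explains why enrollment was simplified; it does not say that samples are missed, and it gives no rate.

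The equal-SD condition is a real limit. IL-6 SDs before the dressing and at 24 h are not given, and the ratios in the table depend on them. Without that condition, all that remains is that the excess variance cannot be negative.

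Finally, an article may leave covariates to a fuller document. That excuses brevity, but not two differing statements of the primary comparison in the text shown.

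**Conclusion.** The inconsistency stands, and it concerns the primary endpoint: level in the abstract and the endpoint section, change in the analysis section, with no stated role for the day-1 sample. It would be too strong to call this bias or two different questions. In the randomized set, level, change and adjusted contrasts have the same expected value, so the harm is an open choice of analysis and avoidable imprecision.

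The change contrast has 1.54 to 1.18 times the variance of the adjusted one over assumed rho of 0.3 to 0.7. This rests on equal SDs, an assumed correlation, and all 46 patients being analysed; the per-protocol set may be smaller. The document supports no firmer figure.

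A reader might also take a baseline covariate and a constrained baseline as interchangeable. They match with complete baselines. When some are missed, a plain covariate model excludes those patients and the constrained model does not. The constrained model, in turn, relies on equal baseline means, which randomization justifies but a set selected on dressing duration after randomization does not guarantee. The point should be corrected before the data are analysed, but it does not invalidate the trial.

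**What to change.** Use one definition in the abstract, Primary endpoints and Statistical analyses: plasma IL-6 at 24 and 48 h after dressing application, compared between arms at each time. State that the mixed model is adjusted for pre-dressing IL-6, by one of two routes:

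1. Baseline IL-6 as a covariate, with a stated rule for missed baselines, such as imputation.
2. A constrained-baseline mixed model, with the pre-dressing, 24 h and 48 h values as responses, a common baseline mean for both arms and treatment-by-time terms after baseline. This keeps patients with a missed baseline and should be fitted to all randomized patients.

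If the per-protocol set stays the main set for mediators, the first route is the safer one there. Use the same model and wording for TNF-α and the other secondary cytokines.

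The cost is a few sentences of analysis text and, for the first route, one missing-data rule. No sample, visit or patient is added.

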### Patient recruitment

Recruitment into the trial will occur in the operating room once the decision has been made by the attending trauma or general surgeon to perform a damage control laparotomy and TAC. We will define an open abdomen as that requiring a TAC due to the abdominal skin and fascia not being closed after laparotomy.

Although no objective, evidence-based indications for damage control laparotomy or open abdominal management exist
[60,61], the Eastern Association for the Surgery of Trauma suggest that this technique may be considered in cases of severe abdominal trauma involving hepatic, non-hepatic, or vascular injuries with intra-abdominal packing; among trauma patients with acidosis (pH ≤7.2), hypothermia (temperature ≤35°C), and clinical coagulopathy or if the patient is receiving massive transfusion; and in patients with severe intra-abdominal infection/peritonitis or necrotizing pancreatitis
[59]. Other indications for the procedure suggested in 2005 by a multidisciplinary expert advisory panel on management of the open abdomen included bowel edema and a significant risk of developing abdominal compartment syndrome
[62].

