### Inclusion criteria

•Age ≥18 years

•Decision made by the attending trauma or general surgeon to perform a damage control laparotomy with application of a TAC device during the index laparotomy

•Requirement for postoperative ICU admission

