### Exclusion criteria

•Age <18 years

•Decision made to perform a definitive or single-stage laparotomy with closure of the abdominal fascia during the index laparotomy

•Administration of intraperitoneal chemotherapy for treatment of intra-abdominal malignancies

•Pregnancy

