Results will be stratified according to the primary indication for damage control laparotomy (intra-abdominal sepsis or abdominal trauma). While clinical efficacy and safety data will be analyzed according to intention-to-treat methods, mediator data will be examined using per-protocol techniques, with per-protocol treatment being defined as the allocated TAC dressing having been in place for at least 24 h. As the number of conducted statistical tests will be large, we will use the false discovery rate (FDR) procedure developed by Benjamini and Hochberg to restrict the proportion of incorrectly rejected null hypotheses to 0.05
[79-81]. All tests will be two-sided, and only those with an FDR-corrected *P* value (that is q-value) <0.05 will be considered statistically significant
[79]. Stata version 12.0 (Stata Corp., College Station, TX, USA) will be used for all analyses.

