This trial has limitations. Although we will be combining the inflammatory mediator concentrations and outcome data for patients with both intra-abdominal sepsis and injury, which may be different, we will stratify our analyses to examine if differences exist between patient diagnoses. Moreover, as the primary objective of this trial is to explore the influence of active abdominal therapy on the systemic inflammatory response among critically ill or injured adults, we will principally use a per-protocol method of analysis. As this method of analysis may not be appropriate or as clinically useful for the exploration of safety and efficacy, we will also utilize an intention-to-treat method of analysis when comparing these endpoints. Importantly, however, as we were unable to estimate the required sample size, we may be underpowered to detect differences in the plasma pro-inflammatory mediator concentrations (or clinical and safety endpoints) among patients randomized to TAC with the ABThera™ *versus* Barker’s vacuum pack.

In conclusion, the Intra-peritoneal Vacuum Trial will be a single-center RCT. Results from this study will lead to an improved understanding of the effect of active negative pressure peritoneal therapy on the systemic inflammatory response to intra-abdominal sepsis or injury after damage control laparotomy. The study will also gather pilot information needed to inform creation of a future multicenter RCT comparing clinical outcomes among those undergoing TAC with the ABThera™ *versus* the Barker’s vacuum pack after damage control laparotomy.

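### Stratifying results by sepsis and trauma does not test whether the dressing effect differs between them, and the two strata need not cover every eligible patient

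*Protocol article*

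**What the plan says.** The Statistical analyses section announces stratification with two levels: "Results will be stratified according to the primary indication for damage control laparotomy (intra-abdominal sepsis or abdominal trauma"). It also says that only tests with an FDR-corrected P value (q-value) below 0.05 count as significant, and that mediator data are analysed per protocol.

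The Discussion, under limitations, concedes that pooled sepsis and injury patients may be unlike each other and offers this remedy: "we will stratify our analyses to examine if differences exist between patient diagnoses".

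The model for the main comparison reads: "we will use a mixed-effects repeated measures linear model to compare the effects of the ABThera™ and Barker’s vacuum pack". It is fitted to plasma IL-6 changes. The article describes no contrast of the dressing effect between indications.

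On who enters the trial, the Inclusion criteria ask for adult age, a need for postoperative ICU care, and "Decision made by the attending trauma or general surgeon to perform a damage control laparotomy with application of a TAC device" at the index laparotomy. Neither sepsis nor injury is required. The only treatment-related exclusion is "Administration of intraperitoneal chemotherapy for treatment of intra-abdominal malignancies"; the others concern age, single-stage closure and pregnancy. The Patient recruitment section reports that an expert panel's further indications included "bowel edema and a significant risk of developing abdominal compartment syndrome". By contrast, the objective in the Background and the Overview describe the population as patients with intra-abdominal sepsis or injury.

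**The concern.** Running the same comparison separately in two subgroups gives two answers to the question of whether the dressing works in that subgroup. Neither answers whether the effect differs between subgroups. If one stratum passes the significance threshold and the other does not, the cause may be chance or unequal stratum size rather than a different effect. With 46 patients in total, this pattern arises easily. The trial is meant to supply pilot information for a multicentre study, so an apparent diagnosis-specific effect should not be reported on weaker evidence than readers will assume.

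The second issue is coverage. A two-level stratification presupposes that every patient is a sepsis case or a trauma case, and the eligibility criteria do not guarantee that. Any patient who is neither would be absent from the stratified results.

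**Working it through.** **What can be reproduced.** Nothing. The Sample size section gives 46 as a convenience sample, with no effect size, SD or power behind it. What follows is an illustration, not a property of the plan.

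**Inputs from the protocol article.** 46 patients, allocation in equal numbers, two-sided tests, and Benjamini-Hochberg control at 0.05.

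**Assumptions.** Stratum split 23/23 (about 11.5 per arm per stratum); one time point; two-sample t-test; independent strata; a true effect of 0.845 SD, identical in both. That effect gives 80.0% power with 23 per arm. It was chosen to describe a trial with reasonable overall power, not taken from the plan.

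**Power in one stratum.** Noncentrality = d × √(n/2) = 0.845 × √(11.5/2) = 2.03, with 2 × 11.5 − 2 = 21 degrees of freedom.
- At two-sided 0.05: power 0.489.
- At two-sided 0.025: power 0.369.

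**Exactly one stratum significant, unadjusted p<0.05.**
- Common effect: 2 × 0.489 × (1 − 0.489) = 0.50.
- No effect: 2 × 0.05 × 0.95 = 0.095.

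**Exactly one stratum significant, Benjamini-Hochberg on these two tests only.** With two tests, exactly one is rejected when its p is at most 0.025 and the other exceeds 0.05.
- Common effect: 2 × 0.369 × (1 − 0.489) = 0.38.
- No effect: 2 × 0.025 × 0.95 = 0.0475, or 4.8%.

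**Sensitivity.** The unadjusted 50% becomes 53% at a 30/16 split and 58% at 34/12. For common effects from 0.4 to 1.0 SD it ranges from 26% to 59% across the three splits. The real FDR family is larger than two tests, so the adjusted figures depend on the other results in it.

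**What an interaction estimate could show.** By the normal approximation, SE of the difference in effect = √(4/n₁ + 4/n₂) SD. The difference detectable with 80% power is (1.96 + 0.84) × SE:

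| Split | SE (SD) | Detectable difference (SD) |
|---|---|---|
| 23/23 | 0.59 | 1.65 |
| 30/16 | 0.62 | 1.73 |
| 34/12 | 0.67 | 1.88 |

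At 23/23, the 95% CI would extend about 1.96 × 0.59 = 1.16 SD either side of the estimate.

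**Coverage.** This is a comparison of texts. The Background and Overview limit the population to sepsis or injury. The Inclusion and Exclusion criteria do not, and Patient recruitment lists indications beyond infection and trauma. The article gives no count of patients outside both groups. If the share were 10% to 30% (assumed), that would be about 5 to 14 of 46.

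**The case against.** Several counter-arguments have force.

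- **The Discussion sentence is ambiguous.** What it says may differ is mediator concentrations and outcomes in sepsis and injury patients. The differences to be examined could be in levels rather than in the dressing effect. This stands as a reading, but the sentence concerns how the trial's analyses are stratified and does not exclude the effect reading. The text should say which is meant.
- **Interaction terms and covariates are usually left to the analysis plan.** This stands for covariates: the article lists none, so no fault follows from indication being absent from the primary model. It does not dispose of the main point, because the article names a method for a stated purpose and, for effect differences, that method does not serve it.
- **Significance is judged by q-values.** This stands. It is why the unadjusted 50% and 9.5% cannot be given alone. If all null hypotheses are true and the tests are independent, Benjamini-Hochberg holds the chance of any rejection in its family to 5%.
- **Bowel edema or compartment syndrome risk may occur in a septic or injured patient,** who then has a stratum. This is true, and the list is outside guidance rather than a set of trial categories. Patients in neither stratum would remain in the combined analysis. The gap is one of wording and classification, and the article does not show that any such patient was enrolled.

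A reader might also infer that chance imbalance in indication goes uncorrected because randomisation is not stratified by it. The documents do not carry that far. Dressing comparisons within a stratum are not confounded by indication, the Discussion explains that randomisation was kept simple to avoid delay, and nothing shows how strongly indication predicts IL-6.

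**Conclusion.** The point holds in a limited form. Stratified results alone cannot show whether the dressing effect differs between sepsis and trauma, and the article offers nothing else for that purpose. Under the assumptions stated, a discordant pair of strata with identical true effects is common (about 50% unadjusted, about 38% with the two-test adjustment) and uncommon with no effect (9.5% and 4.8%). These figures rest on an assumed effect size, split and single time point, none of which the article gives.

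A reader might go further and conclude that the plan will probably declare a spurious diagnosis-specific effect and that this will choose the multicentre population. The article supports neither step. It nowhere says that a differential effect will be claimed from one stratum being significant and the other not. It describes the pilot purpose as feasibility, safety and design deficiencies, and it concedes that power may be low.

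The coverage gap is real but smaller: eligibility and the described population do not match, and the two strata inherit that mismatch.

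**What to change.** In Statistical analyses:

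1. Fit one model in all analysed patients with primary indication as a fixed effect.
2. Base any statement about a differential dressing effect on the treatment-by-indication estimate with its 95% CI, labelled exploratory.
3. Present stratum estimates descriptively, without significance claims of their own.
4. Classify the recorded primary indication as sepsis, trauma or other, blind to allocation and outcome, so that every patient has a category.

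In the Discussion, say whether the differences to be examined are in mediator levels and outcomes, in the dressing effect, or both.

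The cost is small. The indication for damage control laparotomy is already collected (Clinical data), so this is analysis wording plus one blinded classification. A new eligibility criterion or classification at randomisation is not a practical alternative: Trial status reports 37 of 46 patients already enrolled, and neither could apply to them. The drawback is that the interaction estimate will be imprecise, with about 1.65 SD detectable with 80% power at 23/23 and larger differences needed at uneven splits. A small "other" group would support description only.

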## Methods/Design

### Overview

The Intra-peritoneal Vacuum Trial is a single-center RCT, which will intraoperatively allocate critically ill or injured adults to TAC with either the ABThera™ or Barker’s vacuum pack after damage control laparotomy for intra-abdominal sepsis or injury. Although the trial in itself may not be sufficient to establish superiority of the ABThera™ over the Barker’s vacuum pack, we hypothesize superiority, and will examine for evidence of this in hypothesis tests. The CONSORT flow diagram
[57] and an overview of the study design are presented in Figures 
1 and
2, respectively.

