#### Reoperation and TAC dressing changes

Although the allocated TAC dressings will be left in place for a duration determined by the attending surgeon, local FMC and international guidelines suggest re-operation with attempts at abdominal fascia closure between 24 and 72 h after initial application
[53,59,62]. If abdominal fascial closure is not safe or possible at this time, then a TAC dressing change is recommended
[53,62]. Surgeons will be free to utilize any TAC device that they feel is most appropriate at the time of the first and all subsequent dressing changes.

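### The primary IL-6 comparison uses a per-protocol set defined after randomisation, with no intention-to-treat analysis of IL-6 stated, and its 24 h rule does not secure exposure at the 48 h sample

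*Protocol article*

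**What the plan says.** Under Statistical analyses, the populations are split by type of data. On one side, "clinical efficacy and safety data will be analyzed according to intention-to-treat methods". On the other, "mediator data will be examined using per-protocol techniques, with per-protocol treatment being defined as the allocated TAC dressing having been in place"; the minimum duration set there is 24 h. The Figure 2 legend repeats the 24 h definition.

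The limitations in the Discussion confirm that this is intended for the primary objective: "we will principally use a per-protocol method of analysis". The next sentence there adds that "we will also utilize an intention-to-treat method of analysis when comparing these endpoints", and the endpoints meant are safety and efficacy. No intention-to-treat analysis of IL-6 appears anywhere in the article.

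Under Primary endpoints, however, "the primary endpoint is the difference in the plasma concentration of IL-6 at 24 and 48 h after dressing application between patients randomized to TAC" using one dressing or the other. The Overview adds that "we hypothesize superiority, and will examine for evidence of this in hypothesis tests".

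The section on reoperation and dressing changes leaves the duration of the allocated dressing to the attending surgeon and cites guidance for re-operation at 24 to 72 h. It then says: "Surgeons will be free to utilize any TAC device that they feel is most appropriate at the time of the first" dressing change and at every later one.

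**The concern.** The endpoint is worded as a contrast between randomised groups, but the analysis set is formed by what happened in the first 24 h. A patient whose dressing comes off early, for example at an unplanned re-operation, leaves the primary analysis. Three features of the design make this selection matter.

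- **It may track the outcome.** The Background and Table 1 link higher IL-6 to organ dysfunction, complications and death, so patients who deteriorate early plausibly have high IL-6.
- **It may differ by arm.** The allocation is announced in the operating room and the surgeon applies the dressing. The article describes blinding only for the laboratory investigator. The Secondary endpoints section itself raises compartment syndrome and fistula as possible effects of negative pressure therapy.
- **The exposure contrast is incomplete.** A patient who satisfies the 24 h rule may be closed, or wearing the other arm's device, at the 48 h primary sample.

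At stake is whether a difference in IL-6, or the lack of one, reflects the dressing or the patients who were dropped, in a trial of 46.

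**Working it through.** **Inputs.** From the document: 46 patients (a convenience sample), block randomisation to equal groups (23 per arm), primary samples at 24 and 48 h, a blood sample just before the dressing is applied, and re-operation expected at 24 to 72 h. The plan gives no effect size, SD, power or early-removal rate, so it has no figure to reproduce. Everything on bias below is an assumption.

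**1. Exposure at 48 h.** If first re-operations were spread evenly over 24 to 72 h (assumption), the share before 48 h is (48 − 24)/(72 − 24) = 24/48 = 50%. The document gives no actual distribution.

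**2. Precision.** The detectable difference at 80% power, two-sided 5%, is (1.960 + 0.842) × √(2/n) SD.

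- n = 23 per arm: 2.802 × √(2/23) = 0.83 SD
- n = 20 per arm (assumed loss): 0.89 SD
- n = 18 per arm (assumed loss): 0.93 SD

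**3. Selection with no true effect.** Latent severity S drives log IL-6 as Y = rS + √(1 − r²)e, with r = 0.5, 0.7 or 0.9. The most severe patients are removed from each arm. The unadjusted test is a t-test. The adjusted test adds a baseline value B built like Y with its own error. The shift favours the arm that lost more patients. Ranges run over r.

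| Dropped per arm of 23 | Unadjusted shift (SD) | Type I error | Adjusted shift (SD) | Type I error |
|---|---|---|---|---|
| 3 vs 3 | 0.00 | 6–8% | 0.00 | 5–6% |
| 2 vs 1 | 0.04–0.07 | 6–7% | 0.01–0.03 | 5–6% |
| 5 vs 2 (22% vs 9%) | 0.10–0.18 | 7–13% | 0.05–0.09 | 6% |
| 6 vs 1 (26% vs 4%) | 0.17–0.30 | 9–20% | 0.07–0.14 | 7–8% |

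The 3 vs 3 row shows that part of the unadjusted error inflation is not bias. Deleting a fixed number of extreme patients narrows the observed spread more than the true variability of the mean.

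With an assumed SD of 1.5 on the natural-log scale, 0.30 SD is a spurious geometric mean ratio of exp(−0.30 × 1.5) = 0.64, and 0.14 SD is exp(−0.14 × 1.5) = 0.81.

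**4. A second model.** Here early loss is probabilistic. Severity correlates 0.6 with log IL-6 and 0.7 with the liability to lose the dressing early, and there is no baseline adjustment.

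| Loss by arm | Relation to severity | Absolute shift (SD) | Type I error |
|---|---|---|---|
| 10% vs 10% | same in both arms | 0.00 | 5.3% |
| 10% vs 20% | same in both arms | 0.06 | 5.4% |
| 0% vs 20% | same in both arms | 0.15 | 7.4% |
| 10% vs 10% | opposite in the arms | 0.16 | 8.2% |
| 10% vs 20% | opposite in the arms | 0.23 | 10.6% |
| 10% vs 30% | opposite in the arms | 0.29 | 14.4% |

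The t-test on all randomised patients stayed at 4.6% to 5.4% throughout. Equal numbers lost are reassuring only if the reasons are alike in both arms.

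**The case against.** The choice is deliberate and disclosed. The Discussion presents the primary objective as an exploration of mechanism and keeps intention-to-treat for clinical endpoints. The Overview concedes that the trial may not establish superiority, and its pilot role is stated. That tempers the consequences. It does not make the comparison randomised, superiority tests remain planned, and the limitations name low power but not selection. Nor is this a detail left to a fuller plan, because the article fixes the population itself.

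The planned model concerns changes in IL-6, and a pre-dressing sample exists, so the unadjusted figures overstate the likely bias. This stands. In the first model a pure change score would remove the bias altogether, because S enters Y and B equally and cancels. That result depends on the assumption: early removal happens after baseline, and later deterioration is not captured by the baseline sample.

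The unequal scenarios are severe. Planned re-operation falls at or after 24 h, so loss before 24 h should be mostly unplanned and may be rare. This also stands.

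The article never claims that 24 h of wear makes the 48 h value on-treatment, and a minimum exposure can be a coherent definition. The 48 h point is therefore secondary. It shows that the rule gives up randomisation without securing the exposure contrast at both primary time points.

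**Conclusion.** The defect holds on the text. The primary analysis set is defined by a surgeon-decided event after randomisation, no intention-to-treat analysis of IL-6 is stated, and this conflicts with an endpoint defined between randomised patients and tested for superiority. It should be settled before the mediator data are compared.

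The size is uncertain. It runs from about 0 SD when losses are equal and alike, through 0.05 to 0.14 SD (type I error 6% to 8%) for strongly unequal loss with baseline adjustment, to 0.10 to 0.30 SD (about 7% to 20%) without it. All of this assumes severity-driven exclusion and 23 per arm.

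A reader might infer more than the document supports:

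- **That the result will be biased towards one dressing.** No early-removal rates by arm are given, so neither direction nor size can be derived.
- **That a false-positive rate near 20% is expected.** That is the extreme case: 6 vs 1 lost, correlation 0.9, no use of baseline.
- **That half of the 48 h values are off-treatment.** That rests on an assumed even spread of re-operations.
- **That intention-to-treat would recover every patient.** Those who die before 24 h have no later IL-6 under either analysis, and delayed consent also limits usable data.

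**What to change.** In Statistical analyses, the Figure 2 legend and the limitations paragraph of the Discussion:

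1. Make intention-to-treat the primary analysis of IL-6 and the secondary mediators. Include all randomised patients with usable data, by allocated dressing, whatever the dressing duration, closure or device switch.
2. Keep the 24 h per-protocol set as a supportive analysis.
3. Treat any set that requires the allocated dressing still to be in place at 48 h as a labelled sensitivity analysis only. It conditions on a further event after randomisation and may select more strongly.
4. Report by arm, with reasons, the exclusions from each set and the deaths before the 24 h and 48 h samples.

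The cost is wording. Blood sampling is not scheduled conditionally on the dressing staying on, so no new data collection is needed, and the clinical rules on re-operation and dressing changes are untouched. The price is some dilution of the effect from early removal or switching. The supportive analysis can show how much this matters, read with its selection in mind.
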